## Abstract

**Background:**

The chronic pain of patients with knee osteoarthritis (KOA) seriously affects their quality of life and leads to heavy social and economic burden. As a nondrug therapy in Traditional Chinese Medicine (TCM), Tuina is generally recognised as safe and effective for reducing the chronic pain of KOA. However, the underlying central mechanisms of Tuina for improving the pain of KOA are not fully understood.

**Methods/design:**

This study will be a randomised controlled trial with a parallel-group design. A total of 60 eligible participants will be assigned to the Tuina group or healthcare education group (Education group) at 1:1 ratio using stratified randomisation with gender and age as factors. The interventions of both groups will last for 30 min per session and be conducted twice each week for 12 weeks. This study will primarily focus on pain evaluation assessed by detecting the changes in brain grey matter (GM) structure, white matter (WM) structure, and the cerebral functional connectivity (FC) elicited by Tuina treatment, e.g., thalamus, hippocampus, anterior cingulate gyrus, S1, insula, and periaqueductal grey subregions (PAG). The two groups of patients will be evaluated by clinical assessments and multimodal magnetic resonance imaging (MRI) to observe the alterations in the GM, WM, and FC of participants at the baseline and the end of 6 and 12 weeks’ treatment and still be evaluated by clinical assessments but not MRI for 48 weeks of follow-up. The visual analogue scale of current pain is the primary outcome. The Short-Form McGill Pain Questionnaire, Western Ontario and McMaster Universities Osteoarthritis Index, 36-Item Short Form Health Survey, Hamilton Depression Scale, and Hamilton Anxiety Scale will be used to evaluate the pain intensity, pain feeling, pain emotion, clinical symptoms, and quality of life, respectively. MRI assessments, clinical data evaluators, data managers, and statisticians will be blinded to the group allocation in the outcome evaluation procedure and data analysis to reduce the risk of bias. The repeated measures analysis of variance (2 groups × 6 time points ANOVA) will be used to analyse numerical variables of the clinical and neuroimaging data obtained in the study. *P*<0.05 will be the statistical significance level.

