### Sample size

Sample size is required to compare two group mean values. The calculation method of bilateral equality of two samples is adopted [56] for two groups of A = Tuina group and B = Education group. Suppose H0: μA−μB=0, H1: μA−μB≠0. According to previous relevant research and pre-experiment results [39, 57], we expect the VAS significant score difference between and after 12 weeks of Tuina as μA = 3, and the VAS score difference between and after healthcare education intervention as μB = 0.7, assuming that the standard deviation *σ* of the two groups is equal, i.e., *σ*=2.1. If we set *α*=0.05 as the type I error, *β*=0.10 as the type II error, and 1−*β*=0.90 as the power, the final result is that we need at least 25 samples in each group. For the primary outcome, VAS will be assessed at baseline and at the end of 6 and 12 weeks of treatment, followed by 12, 36, and 48 weeks of follow-up. The statistical significance is defined as *P* < 0.05, and the 95% confidence interval will be reported.

Many MRI studies have reported statistical significance with 12 to 21 patients per group [23, 58–60]. To have a powerful and repeatable statistical effect, we require 25 patients per group in this trial. Considering a 20% dropout rate and the possible excessive head motion during scanning, it will include 30 KOA participants in each group. In summary, we plan to enroll 60 participants, and each group will undergo MRI scans to investigate different central mechanisms between Tuina and healthcare education treatments.

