### Interventions

The participants will receive a total of 24 treatments in 12 weeks. The interventionists, who hold a PhD, must have at least 10 years of experience with Tuina treatment and be skillful in healthcare education for the participants. They are also required to have passed a clinical test to ensure consistency of the trial. The clinical test primarily includes the time of Tuina, the positioning of the treatment site, and the application of specific Tuina manipulation types. The standard operating procedures primarily include Tuina’s time, treatment site, and manipulation category, as well as the time and content of health education. In the process of Tuina or Education intervention, the two groups will not allow any concomitant medications or other interventions. However, concomitant medications or other interventions can be used during subsequent follow-up, and the treatment will be recorded in detail.

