#### Primary outcome measurement

The primary outcome measurement is VAS [74]. VAS is used to assess the current degree of pain. VAS is a 10-point scale selected to quantitatively measure the level of KOA pain during the study, for which 0 means no pain and 10 means unbearable pain. The VAS mean scores will be assessed by repeated longitudinal analysis. The single timepoint of the primary interest for the comparison is week 12.

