### Statistical analyses

Clinical data will be analysed through the intention-to-treat assumption. For all outcomes, we use longitudinal models where participant outcomes and treatments are collected at a multiple follow-up times. Moreover, participants who meet the suspension criteria will be removed from the trial, and the modified intention-to-treat analysis will be adopted. For the missing data, several sensitivity analyses will be conducted to evaluate their effects on the results of the experiment. All analyses were performed with SPSS 21.0 statistical software (IBM, Armonk, NY, USA) by statisticians who are blinded to the group allocation.

The baseline characteristics will be expressed with descriptive statistics for the two groups, which are reported as the mean ± standard deviation. A Kolmogorov–Smirnov test with Lilliefors correction will be used to analyse all quantitative variables to determine whether they follow a normal distribution. Parametric statistics (Tukey test) or nonparametric statistics (Wilcoxon rank-sum test) will be used for the within- and between-group analyses in accordance with the results of the homogeneity and normality analyses. When the initial homogeneity and normality of data distribution are found, repeated-measure ANOVA will be implemented, or the Friedman test and Kruskal–Wallis test will be used when initial homogeneity but non-normality of data distribution is found, or only linear mixed model will be adjusted for age and gender if the initial homogeneity is not found. Adverse events in each group will be documented as percentage for safety assessments by using the chi-square test or Fisher’s exact test. Statistical significance is defined as *P* < 0.05, and the 95% confidence interval will be reported.

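### Week 12 is declared the primary VAS time point, but no stated test is tied to it: the default is an omnibus repeated-measures ANOVA over all six visits, chosen by assumption checks

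*Protocol article*

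**What the plan says.** All references are to the protocol article.

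- **Outcome and time point.** The abstract states: "The visual analogue scale of current pain is the primary outcome". Primary outcome measurement adds: "The single timepoint of the primary interest for the comparison is week 12". It also says that VAS means will be assessed by a repeated longitudinal analysis, without naming a model or a contrast.
- **Sample size.** The trial is sized as a two-sided, two-sample comparison of VAS change over 12 weeks (3 against 0.7, SD 2.1). VAS is "assessed at baseline and at the end of 6 and 12 weeks of treatment, followed by 12, 36, and 48 weeks of follow-up", which makes six visits.
- **Analysis in the abstract.** "The repeated measures analysis of variance (2 groups × 6 time points ANOVA) will be used to analyse numerical variables" of both the clinical and the neuroimaging data.
- **Analysis in the Statistical analyses section.** "When the initial homogeneity and normality of data distribution are found, repeated-measure ANOVA will be implemented". If the data are homogeneous but not normal, Friedman and Kruskal–Wallis tests replace it. The third branch reads "or only linear mixed model will be adjusted for age and gender if the initial homogeneity is not found". Tukey or Wilcoxon rank-sum tests are also listed for within- and between-group analyses, with no time point given. The section declares intention-to-treat, modified for suspended participants, and plans sensitivity analyses for missing data.
- **Follow-up.** Interventions states that "concomitant medications or other interventions can be used during subsequent follow-up, and the treatment will be recorded in detail".

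**The concern.** The declared question is one contrast: Tuina against Education at the end of 12 weeks of treatment. A 2 × 6 repeated-measures ANOVA yields two group-related F tests, and neither is that contrast.

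- The group main effect compares the mean of all six visits. It includes baseline, where randomisation makes the expected difference zero.
- The group-by-time interaction asks whether the difference varies over the six visits. Any visit can drive it, and three of the six fall in a period when other treatment is allowed.

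The article does not say which F test decides. The P value reported for the primary outcome could therefore be significant with no week-12 effect, or not significant with one. Because the branch is chosen from the observed data, even the type of test is not fixed in advance.

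A second issue is missing visits. Classical repeated-measures ANOVA uses only participants with every visit. A missed follow-up visit would then remove a week-12 score already in hand, which does not fit the intention-to-treat statement.

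**Working it through.** **1. The plan's own figure.** Inputs from Sample size: difference 3 − 0.7 = 2.3, SD 2.1, two-sided alpha 0.05, power 0.90.

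n per group = 2 × (1.960 + 1.282)² × 2.1² / 2.3² = 2 × 10.51 × 4.41 / 5.29 = 17.5, so 18. With the t distribution it is 19.

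The article states 25, so its figure is not reproduced. The discrepancy is on the safe side and does not bear on this point. A direct week-12 comparison of change has 96.7% power at 25 per group and 96.0% at 24 (30 less 20%), using the t distribution.

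**2. What the group main effect estimates.** It is the mean of the six visit differences. The trajectories below are assumptions, in the order baseline, week 6, week 12, then three follow-up visits.

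- 0, 1.15, 2.3, 0, 0, 0: mean 3.45/6 = 0.575. Simulated power 13 to 24%.
- 0, 1.15, 2.3, 1.15, 1.15, 1.15: mean 6.9/6 = 1.15. Simulated power 37 to 70%.

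The ranges cover correlations 0.5 and 0.7, with 25 per arm complete or 30 per arm with 5% missed visits. A week-12 test of change has 96 to 98% and 97 to 99% power in the same runs.

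**3. What drives the interaction.** With equal correlation between visits, the interaction F has 5 and 5 × (2n − 2) degrees of freedom and noncentrality

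λ = (n/2) × Σ(d_t − d̄)² / [σ²(1 − ρ)].

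The SD of change is 2.1, so 2σ²(1 − ρ) = 4.41 and the denominator is 2.205.

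- *No week-12 effect, 1.5 points at each follow-up visit, n = 30.* d̄ = 0.75, Σ = 6 × 0.5625 = 3.375, λ = 15 × 3.375/2.205 = 22.96. The interaction is significant in 97% of trials; a week-12 test in about 5%.
- *Planned 2.3 at week 12, half of it persisting, n = 25.* d̄ = 1.15, Σ = 2 × 1.3225 = 2.645, λ = 12.5 × 2.645/2.205 = 14.99. Power 86%; simulation gives 81 to 87% across the settings in step 2.
- *Planned 2.3 at week 12, nothing in follow-up, n = 25.* Σ = 6.6125 − 6 × 0.575² = 4.629, λ = 26.24. Power 99%; simulation gives 98 to 99%.

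**4. A smaller effect with missing visits.** Assume 1.2 points at week 12, 10% missing by then and a further 12% later: 27 per arm at week 12 and 30 × 0.78 = 23.4 with all six visits.

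- *0, 0.6, 1.2, 0.6, 0.6, 0.6.* Σ = 0.72, λ = 11.7 × 0.72/2.205 = 3.82, power about 27% (26% at the low end of the simulations).
- *0, 1.2, 1.2, 0, 0, 0.* Σ = 2.88 − 6 × 0.4² = 1.92, λ = 10.19, power about 67%.
- *Week-12 comparison, correlation 0.5.* Change score: SE = 2.1 × √(2/27) = 0.572, power about 54%. Adjusted for baseline: residual SD = 2.1 × √(1 − 0.25) = 1.819, SE = 0.495, power about 66% by formula and 63 to 65% in simulation.

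**5. Participants with all six visits.** If each of the five post-baseline visits is missed independently with probability q (assumed), the complete share is (1 − q)⁵.

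- q = 2%: 90%, about 27 of 30 per arm.
- q = 5%: 77%, about 23 of 30.
- q = 10%: 59%, about 18 of 30.

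At 5% the number is already below the plan's own 25, though not below the 18 or 19 that its inputs require.

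**The case against.** Four counter-arguments deserve weight.

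- **The ANOVA is not fixed.** A reader might infer that the primary VAS analysis simply is the 2 × 6 ANOVA. The abstract sentence covers all numerical variables, and the Statistical analyses section makes repeated-measures ANOVA one of three branches. This stands. The fault is that no single primary test is fixed and that the default branch is the ill-fitting one.
- **Week 12 could still be tested.** A reader might infer that the plan cannot test week 12. The article names week 12, and the listed Tukey or Wilcoxon tests could be applied there. An analysis plan that is not shown may say so. What remains is that the stated analysis does not match the stated comparison, and nothing in the article joins them.
- **Deletion of incomplete cases is not protocol text.** It is a property of classical repeated-measures ANOVA and would not occur in the mixed-model branch. A reader might also infer a biased result. Nothing here quantifies bias, and the article plans sensitivity analyses for missing data, so that claim is not made.
- **The power contrast depends on the trajectory.** With 1.2 points at weeks 6 and 12 and none afterwards, the omnibus test (67%) slightly beats the adjusted week-12 test (64%). The follow-up-only pattern is an illustration that the documents do not predict. Both points stand. At the planned effect, loss of power is a lesser matter; the main harm is a P value that answers another question.

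**Conclusion.** The concern holds in this form: the primary comparison is declared at week 12, the trial is sized for it, and no stated test is tied to it. The default analysis is an omnibus ANOVA whose group effect dilutes the week-12 difference with baseline and follow-up, and whose interaction can be decided by visits at which other treatment is allowed.

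The sizes rest on assumed trajectories, equal correlation between visits and an SD of change of 2.1. A difference confined to follow-up gives about 97% significant interactions against 5% for a week-12 test. For 1.2 points with missing visits, omnibus power runs from about 26 to 67%, against 63 to 65% for a baseline-adjusted week-12 comparison. At 2.3 points the week-12 test exceeds 95%, and the interaction has about 81 to 99%.

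The documents do not support saying that the ANOVA is the only planned analysis, that week 12 cannot be tested, or that the result will be biased.

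**What to change.** For the primary outcome, replace the three-branch rule in Statistical analyses and the 2 × 6 ANOVA sentence in the abstract with one prespecified analysis:

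- A linear mixed model (MIXED in the SPSS version already named) for VAS at weeks 6 and 12. Use categorical time, group, group-by-time and an unstructured covariance, with baseline VAS, age and gender as covariates. Baseline VAS is needed for the 63 to 65% power above; without it, power is about 54%. Age and gender are the stratification factors.
- All randomised participants analysed as allocated. Those with no post-baseline score are handled in the missing-data sensitivity analyses already planned.
- A single primary test: the model-based Tuina minus Education difference at week 12, with its 95% confidence interval.
- Follow-up visits analysed as secondary and labelled as including other treatments.

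In the same abstract sentence, correct the six time points for neuroimaging to three, since the flow chart and study schedule place MRI only at baseline, week 6 and week 12.

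The cost is changed wording and slightly more analysis work. The data and software stay the same, and no extra patients are needed: 18 or 19 per group already give 90% power for the direct week-12 comparison at the planned effect.

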**Fig. 1 Fig1:**
[figure not shown]
Flow chart of the trial. The present study is a randomized controlled trial using multimodal MRI. Sixty KOA patients will be included and randomized equally to two groups, a Tuina group and an Education group. For 30 patients in each group, this trial will include a 12-week treatment period. During the treatment, patients in the Tuina group will receive 24 sessions of Tuina treatments, while the Education group will receive health care education. Both the outcome assessments and MRI scan will be performed at 3 time points, namely the baseline, the end of the treatments at 6 weeks and 12 weeks. Only the clinical outcomes will be assessed during 48 weeks of follow-up subsequently. The central mechanism of Tuina in the treatment of KOA will be analyzed after data collection

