**Fig. 2 Fig2:**
[figure not shown]
Study schedule for data collection. The informed consent and examination will be conducted after recruitment. Then, matched KOA patients will be randomized into two groups and receive treatment. Both clinical outcomes and MRI scans will be performed at 3 time points. Only clinical data will be collected at 48 weeks of follow-up subsequently. Adverse events will be recorded in the case report form at any time during the study. *VAS* visual analog scale, *SF-MPQ* the Short-Form McGill Pain Questionnaire, *HAMD* Hamilton Depression Scale, *HAMA* Hamilton anxiety scale, *WOMAC* the Western Ontario and McMaster Universities Osteoarthritis Index, *SF-36* the Short Form 36 Health Survey scale

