The 3D T1 structure data analysis will be performed with FSL tools (FMRIB Software Library) [71]. SIENAX (part of FSL 5.0) [72] will be used to obtain the volumes of neocortical GM, total GM, and WM. The normalised volumes of subcortical regions such as hippocampus and thalamus will be estimated from FMRIB’s integrated registration and segmentation tool (part of FSL 5.0, FMRIB Software Library) [73]. The cortical thickness at each vertex will be obtained using FreeSurfer (http://surfer.nmr.mgh.harvard.edu). DTI data-processing pipeline will follow the diffusion toolbox in FSL to obtain FA and MD images, and voxelwise tract-based spatial statistics method will be applied to examine FA/MD changes. For the resting-state fMRI data, preprocessing and functional connectivity analyses will be performed with SPM12 software (SPM12, Wellcome Department of Imaging Neuroscience, London, UK; http://www.fil.ion.ucl.ac.uk/spm/) by using MATLAB 2013b (Mathworks, Inc., Natick, MA, USA).

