### Outcome measurements

The clinical outcome will be measured by six self-report questionnaires at baseline and the end of 6 and 12 weeks of treatment, followed by 12, 36, and 48 weeks of follow-up. The responses can reflect the degree of pain, sensation, emotion, and quality of life.

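### The abstract gives the MRI data a six-level time factor although MRI is done at three time points, and P<0.05 for voxelwise and vertex-wise imaging is not said to be a corrected level

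*Protocol article*

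**What the plan says.** The abstract (Methods/design) names a single model for both kinds of data: "2 groups × 6 time points ANOVA) will be used to analyse numerical variables of the clinical and neuroimaging data". Its next sentence adds that P<0.05 "will be the statistical significance level".

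On the MRI schedule the article is consistent. The Fig. 1 legend says "Both the outcome assessments and MRI scan will be performed at 3 time points", and the Fig. 2 legend says "Both clinical outcomes and MRI scans will be performed at 3 time points". The abstract itself has patients scanned at baseline and at the end of 6 and 12 weeks of treatment, after which they will "still be evaluated by clinical assessments but not MRI for 48 weeks of follow-up". The clinical scales are collected "at baseline and the end of 6 and 12 weeks of treatment, followed by 12, 36, and 48 weeks of follow-up" (Outcome measurements).

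The section MRI data acquisition lists six imaging metrics: grey-matter density, cortical thickness, subcortical volumes, FA, MD and functional connectivity. For the diffusion data, a "voxelwise tract-based spatial statistics method will be applied to examine FA/MD changes". Cortical thickness is obtained vertex by vertex in FreeSurfer. Global and subcortical volumes are measured per region. The abstract names six brain regions, as examples.

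The section Statistical analyses repeats the 0.05 level, says longitudinal models are used for all outcomes and that all analyses are done in SPSS, and gives no separate model or threshold for imaging.

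**The concern.** The abstract states a specific model for imaging that the imaging schedule cannot supply with data. This is a contradiction within the document and not a detail left for later.

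The threshold raises a second question. A bare 0.05 can mean a level per test or a level for the whole family of tests. For one clinical scale at one time point the two are the same. For a map tested voxel by voxel, or for several metrics in several regions, they differ greatly.

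The brain-mechanism aims are at stake. Both aims at the end of the Background concern brain changes, the abstract says the study focuses primarily on them, and the Discussion describes the imaging work as confirmatory. The Background also expects to determine the brain area specific to Tuina. A claim of that kind needs a model that matches the data and an error rate that is defined.

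**Working it through.** **1. Time points**

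| Data | Occasions | Count |
|---|---|---|
| Clinical scales (Outcome measurements) | baseline; weeks 6 and 12 of treatment; 12, 36 and 48 weeks of follow-up | 1 + 2 + 3 = 6 |
| MRI (abstract; Study design; legends of Figs. 1 and 2) | baseline; weeks 6 and 12 | 1 + 2 = 3 |

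The stated figure of 6 is reproduced for the clinical scales. For MRI it is not: 3 of the 6 levels, half the cells of the 2 × 6 layout, have no scans.

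**2. Effect on the group-by-time test**

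For g groups, t time points and N complete cases, the degrees of freedom are (g−1)(t−1) and (N−g)(t−1). Take g = 2 and N = 60, the planned total.

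- As stated, t = 6: 1 × 5 = 5 and 58 × 5 = 290.
- As the scans allow, t = 3: 1 × 2 = 2 and 58 × 2 = 116.

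**3. What an uncorrected 0.05 would mean**

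The article does not say that 0.05 is uncorrected, so this step is conditional. For m independent tests with no true effect, the chance of at least one false positive is 1 − 0.95^m, and the expected number is 0.05m.

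| m | Basis | Chance of at least one | Expected number |
|---|---|---|---|
| 6 | six named regions, one metric | 1 − 0.95^6 = 0.265 | 0.3 |
| 36 | six metrics × six regions (illustrative) | 1 − 0.95^36 = 0.842 | 1.8 |

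A Bonferroni level for 36 tests would be 0.05/36 = 0.0014. The 36 is an illustration: the article does not cross every metric with every region, and imaging measures are correlated, which changes the exact chance.

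The documents give no map size for the voxelwise and vertex-wise analyses. With assumed sizes of 1,000, 10,000 and 100,000 elements and no true effect, 0.05 × size gives 50, 500 and 5,000 false positives on average.

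**4. Share of positive findings that would be false**

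This share is a different quantity from those in step 3. If a proportion π of tests have a true effect, the false share among significant results is 0.05(1−π) / [0.05(1−π) + power × π].

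- π = 0.01, power 0.3: 0.0495 / (0.0495 + 0.003) = 94%.
- π = 0.50, power 0.8: 0.025 / (0.025 + 0.40) = 6%.

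The share exceeds one half only when π is below 0.05 / (0.05 + power), which is 5.9%, 9.1% and 14.3% for power 0.8, 0.5 and 0.3. The documents give neither π nor the power for imaging, so the share cannot be fixed.

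**The case against.** The best defence is that this is a slip in a condensed sentence. Six levels is right for the clinical scales, the MRI schedule is stated consistently elsewhere, and the section Statistical analyses mentions repeated-measures ANOVA without a number of levels. That limits the damage but does not remove the error, because the abstract is the only place that gives the imaging data a model with stated dimensions. A reader might infer that imaging cannot be analysed by repeated measures at all. That does not follow, since a 2 × 3 model can be fitted.

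The second defence is that the article never says uncorrected, and that a correction method for imaging is something an article may leave to the full protocol or analysis plan. This stands. The absence of a named correction is not in itself an error, and the tract-based analysis is assigned to its own pipeline and may carry its own correction. What remains is that 0.05 is stated expressly for data that include neuroimaging, without saying which kind of level it is.

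Three further inferences are tempting, and the documents do not support them:

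- That most positive imaging findings would be false. This needs an uncorrected threshold and a small share of true effects, and the article states neither.
- That all imaging tests are voxelwise or vertex-wise. Global and subcortical volumes are not.
- That the six regions form a fixed family. They are given as examples only.

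**Conclusion.** The point holds in two parts of unequal strength. The first is firm: the six-level time factor is wrong for MRI, which has three occasions, and it rests on a count of scheduled visits with no assumption. The second is conditional: 0.05 is the only level given for imaging with many tests, and if it were used uncorrected the family-wise error would be 26% for 6 tests and 84% for 36, assuming independence and no true effects.

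The consequence is confined to the imaging aims. VAS is the primary outcome, with week 12 as the time point of main interest, and that comparison is untouched. The correction is worth making because the mechanism aims are central to the trial and the change is cheap.

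**What to change.** - In the abstract, state 2 groups × 6 time points for the clinical scales and 2 groups × 3 time points for MRI.
- Name the group difference in change from baseline to week 12 as the main imaging contrast.
- State that 0.05 for voxelwise and vertex-wise imaging is a family-wise-error-corrected level, obtained with the standard corrections in FSL, SPM12 and FreeSurfer, and say so in Statistical analyses as well.
- Prespecify a closed list of regional measures and apply a multiplicity correction across it (Holm is one option). The example regions in the abstract could serve as a starting point, but the list has to be fixed by decision.
- Label all other imaging results exploratory.

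The cost is a few sentences and standard options in software already chosen. No visit, scan or sample size changes. The price is some loss of sensitivity for single regions, which a short list keeps small.
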